##### Subjectively Measured Sleep

###### Consensus Sleep Diary

Participants will complete the Consensus Sleep Diary (Carney et al., 2012) daily during the intervention period and whenever wearing the Actiwatch Spectrum Plus. The Consensus Sleep Diary includes questions about time to bed, time to sleep, number and duration of nighttime awakenings, time of final awakening, time out of bed, and overall sleep quality. Diary data will guide the weekly sleep opportunity window for those receiving sleep restriction. It will also be used in conjunction with the actigraphy log to facilitate actigraphy scoring, as described above (Ancoli-Israel et al., 2015).

###### Perceived Sleep Quality

The eight-item Patient Reported Outcomes Measurement Information System (PROMIS) Sleep Disturbance Short Form 8a (Yu et al., 2012) will be used to assess perceived sleep quality at baseline, post-intervention, and 3-month follow-up. Respondents rate the quality of their sleep over the prior 7 days on a five-point scale ranging from *Very poor* to *Very good* and rate the frequency with which they experienced different sleep symptoms on a five-point scale ranging from *Not at all* to *Very much*. Higher scores reflect worse sleep quality. All PROMIS assessments generate *T* scores that are standard scores with a mean of 50 and a standard deviation of 10 based on the reference population in which the measure was developed. For many PROMIS measures this is the general United States population; however, the Sleep Disturbance scale was developed with a population enriched for chronic illness. Thus, a score of 50 on this scale represents the average for individuals slightly more impaired than the general population.

###### Sleep-Related Daytime Impairment

The eight-item PROMIS Sleep-related Impairment Short Form 8a (Yu et al., 2012) will assess perceived impairment during wake associated with sleep problems at baseline, post-intervention, and 3-month follow-up. Respondents rate the frequency with which they experienced daytime sleep-related symptoms over the prior 7 days on a five-point scale ranging from *Not at all* to *Very much*. Higher scores indicate greater daytime impairment. The PROMIS Sleep-related Impairment scale was also developed with a population enriched for chronic illness, and thus scores can be interpreted similarly to the Sleep Disturbance scale.

#### Secondary Outcomes

##### Health-Related Quality of Life

The 27-item Functional Assessment of Cancer Therapy – General (FACT-G) (Webster et al., 2003) will measure HRQOL at baseline, post-intervention, and 3-month follow-up. Participants indicate the extent to which each item has applied to them over the past week using a five-point scale ranging from *Not at all* to *Very much*, with higher scores indicating better HRQOL. The measure yields four subscales reflecting physical, social, emotional, and functional well-being, which can be summed to yield a total score.

##### Symptom Burden

###### The Memorial Symptom Assessment Scale

The 32-item Memorial Symptom Assessment Scale (MSAS; Portenoy et al., 1994) will evaluate overall symptom burden at baseline, post-intervention, and 3-month follow-up. The MSAS measures the prevalence of, severity of, and distress associated with 32 physical and psychological symptoms over the course of the past week. Frequency of symptoms is rated on a four-point scale ranging from *Rarely* to *Almost constantly*, severity of symptoms is rated on a four-point scale ranging from *Mild* to *Very severe*, and symptom-related distress is measured on a five-point scale ranging from *Not at all* to *Very much*. The measure yields three sub-scales reflecting physical symptom burden, psychological symptom burden, and overall distress. A total score can also be computed, with higher scores indicating greater symptom burden.

##### Patient Reported Outcomes Measurement Information System-Cancer Computer Adaptive Tests

Symptoms of fatigue (Lai et al., 2011), anxiety (Pilkonis et al., 2011), and depression (Pilkonis et al., 2011, 2014) will be assessed at baseline, post-intervention, and 3-month follow-up with PROMIS-Cancer computer adaptive tests. The PROMIS-Cancer scales were derived from established PROMIS item banks and were refined to increase the cancer-relevance of the measures (Garcia et al., 2007). For all constructs, respondents rate their symptom experience over the past 7 days on a five-point scale ranging from *Never* to *Always.* Select items in the Fatigue item bank use a five-point scale ranging from *Not at all* to *Very much* or from *None* to *Very.* Across all item banks higher scores indicate greater symptom burden.

#### Urine

Urinary 6-sulfatoxymelatonin (aMT6s), the primary urinary metabolite of melatonin, will be measured at baseline, post-intervention, and 3-month follow-up as a marker of circadian rhythms. The night prior to each assessment participants will collect three urine samples: pre-bedtime, overnight including the first morning void, and approximately 3 h after the first morning void (Cook et al., 2000). For each sample, total volume will be recorded, aMT6s and creatinine will be determined, and the concentration of aMT6s will be calculated and expressed as μg/g Cr (Schernhammer and Hankinson, 2009).

#### Adherence

In Part 1 of the study, participants will provide information about protocol adherence in the semi-structured interview and accompanying survey. In both parts of the study, adherence to sleep restriction and stimulus control instructions will be gathered by self-report and from the Consensus Sleep Diaries that participants will complete daily during the 6-week intervention period. Re-Timer™ usage and reasons for non-adherence will be recorded on a daily Re-Timer™ log (Fox et al., 2021).

### Analytic Plan

Across both parts of the study, descriptive statistics will be used to characterize the sample.

#### Part 1: Qualitative Approach

For Part 1 of the study, two coders will review the semi-structured interview transcripts and independently generate a preliminary list of themes regarding barriers and facilitators of treatment adherence using a constant comparative approach (Glaser and Strauss, 1967). The coders will meet regularly to discuss and compare themes. Redundant and irrelevant themes will be removed, and a coding dictionary will be developed for the remaining analysis. Coders will use this dictionary to code all transcripts, and data saturation will be evaluated. Past work indicates that saturation often occurs within the first 12 interviews, and basic themes may be identifiable as early as the sixth interview (Guest et al., 2006). Therefore, 15 interviews will be conducted to increase the likelihood of reaching saturation. Results, consisting of the most prevalent and important themes and corresponding quotations from participants, will inform any needed modifications to the delivery of the candidate intervention components to enhance adherence in Part 2.

#### Part 2: Intervention Optimization

For Part 2, we will use benchmarks of 80% recruitment (i.e., 80% of eligible survivors) and 80% retention to demonstrate feasibility. We will use a benchmark of 60% protocol adherence for each candidate intervention component, based on prior studies of CBT-I and bright light in cancer survivors (Berger et al., 2003; Ancoli-Israel et al., 2012). Descriptive statistics will be applied to the FACIT-TS-G items to examine acceptability.

To identify the optimal combination of candidate intervention components, longitudinal mixed effects models will be fit to the data with primary and secondary outcomes evaluated in separate models. All study time points will be included in these models, and fixed effects will include time (a nominal variable with three levels, which will be entered as two indicator variables), each candidate intervention component, and two-way interactions among components. The effect of a component at post-intervention and 3-month follow-up will be assessed based on that component’s interaction with time. Candidate intervention components will be defined using effect coding (absence: −1, presence: +1) so effects remain uncorrelated (Kugler et al., 2012). Models will also adjust for hypothesized covariates as outlined above, as well as demographic and baseline clinical characteristics found to significantly differ across conditions. Further analyses will evaluate if the presence of multiple candidate intervention components has a greater effect on each outcome than single components. To do this, an additional variable will be created to indicate the number of components to which a participant was exposed (0, 1, 2, 3). This variable will be included as a fixed effect in these models, along with its interaction with time.

In addition to optimizing the intervention, we will also explore the potential mediating role of circadian markers (i.e., aMT6s, circadian activity rhythms, sleep regularity) on the effects of candidate intervention components. The potential mediating role of sleep disturbance on the relationships of intervention components to HRQOL and symptom burden will also be evaluated. Given the exploratory nature of this analysis, interpretation will focus on effect sizes rather than statistical significance.

Power analyses for Part 2 were conducted using the Factorial Power Plan Macro for SAS (Dziak et al., 2013) to detect an effect size ≥0.40 for main effects and two-way interactions with 80% power and two-sided alpha = 0.05. Analyses will be conducted using a maximum likelihood estimation approach, which provides valid inference in the presence of missing data under a missing at random assumption (Enders and Bandalos, 2001). Once all data are collected, they will be imported into SPSS (IBM, Armonk, NY, United States) (IBM Corp, 2020) for cleaning. Data will then be analyzed in SPSS (IBM Corp, 2020), and MPlus (Muthén & Muthén, Los Angeles, CA, United States) (Muthén and Muthén, 1998-2017).

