
A leading theory of sleep-wake regulation is the two-process model (Borbely et al., 2016), which posits that sleep timing and intensity depend on the interaction of a homeostatic process and a circadian process, which function independently. According to this model, the homeostatic process reflects the body’s attempts to maintain balance, in that more time spent awake leads to increased pressure to fall asleep (Deboer, 2018). The circadian process, a pacemaker managed by the suprachiasmatic nucleus of the hypothalamus, determines one’s daily rhythm for sleep and wake, leading to increased sleepiness at certain times of the day and increased alertness at others (Deboer, 2018). Thus, sleep-wake cycles and circadian rhythms separately influence sleep (Borbely et al., 2016). Sleep restriction and stimulus control, the two core components of CBT-I, both target the homeostatic process. Conversely, systematic bright light exposure targets the circadian process. Therefore, combining sleep restriction, stimulus control, and bright light may have additive or even interactive effects. One known study is currently exploring this hypothesis (Bean et al., 2020); however, it is doing so exclusively among patients undergoing chemotherapy for breast cancer. Thus, the applicability of results to cancer survivors who have completed primary treatment will be unclear. Additionally, this known study is adding systematic bright light exposure to CBT-I as a packaged intervention, thus increasing the burden associated with this already challenging treatment. To maximize benefit from the available evidence-based treatments, studies are needed that can determine what combination of behavioral sleep intervention components yields the most effective intervention while also maximizing adherence to optimize impact.

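### As written, the two-way component interactions are not crossed with time, so each averages in the pre-treatment visit and none is specific to post-intervention or 3 months

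*Protocol article*

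**What the plan says.** All statements are in the protocol article. Except where noted, they stand under Part 2: Intervention Optimization.

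- Visits: "All study time points will be included in these models". Time is nominal with three levels, so baseline is an outcome row and not a covariate.
- Treatment terms listed as fixed effects: "each candidate intervention component, and two-way interactions among components".
- Use of time: "The effect of a component at post-intervention and 3-month follow-up will be assessed based on that component’s interaction with time".
- Coding: "Candidate intervention components will be defined using effect coding", with −1 for absence and +1 for presence.
- A separate further analysis uses a count of components received, from 0 to 3: "This variable will be included as a fixed effect in these models, along with its interaction with time".
- Power: 80% at two-sided alpha 0.05 for an effect size of at least 0.40, claimed for main effects and two-way interactions alike.

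The Introduction gives the reason for looking at interactions: "combining sleep restriction, stimulus control, and bright light may have additive or even interactive effects". The Discussion presents the ability to explore them as an advantage over earlier comparative designs.

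**The concern.** When baseline is an outcome, a treatment effect shows only as a departure from baseline. The plan applies this to main effects by reading them from component-by-time terms, and it crosses the count variable with time as well. Of the three kinds of treatment term in the section, only the component-by-component terms receive no crossing.

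An uncrossed interaction is assumed equal at all three visits. Before treatment its expectation is zero, so the fitted value is a weighted average of zero and the effects of interest. It is not the interaction at post-intervention, nor the one at 3 months.

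This model is meant to identify the best combination of components. A diluted interaction can hide two components that reinforce or undercut each other, and so affect which are kept. The count variable cannot stand in, because it does not distinguish which pair a participant received.

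**Working it through.** **Inputs from the protocol article.** 80 participants in Part 2 (Participants and Recruitment); eight conditions and contrasts of 40 against 40 (Study Design); three visits, −1/+1 coding, effect size 0.40, two-sided alpha 0.05 (Part 2: Intervention Optimization). Under this coding the product of two components also splits the sample 40 against 40.

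**Assumptions.** Unit variance at each visit, 10 participants per condition, and a within-person correlation r, which the article does not give and which is therefore varied. Effects are on the mean-difference scale; a difference of 0.40 SD is a coefficient of 0.20.

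**The plan's own power figure.** A 0.40 SD difference with 40 against 40 at a single visit has standard error √(2/40) = 0.224 and power of about 43%. If 0.40 is instead a −1/+1 coefficient (a difference of 0.80), power is 94–95%. About 80% is reached with r ≈ 0.77 (baseline-adjusted) or r ≈ 0.80 (change score). The stated 80% therefore cannot be reproduced without an unstated input.

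**Expected value of the uncrossed term.** In the balanced design the generalised least squares estimate is a weighted mean of the interaction at the three visits.

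- Compound symmetry, equal weights, sustained interaction: (0 + 0.40 + 0.40)/3 = 0.267, or two thirds.
- Compound symmetry, post-intervention only: (0 + 0.40 + 0)/3 = 0.133, or one third.
- First-order autoregressive with lag-1 correlation 0.6, weights 1 : 0.4 : 1. Sustained: 0.40 × 1.4/2.4 = 0.233. Post-intervention only: 0.40 × 0.4/2.4 = 0.067.

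A simulation of 3,000 trials at r = 0.5 under compound symmetry gave mean coefficients of 0.136 (sustained; expected 0.133) and 0.064 (post-intervention only; expected 0.067). With the interaction crossed with time, the sustained case gave 0.197 at each follow-up (true value 0.20). The post-intervention-only case gave 0.196 and −0.003 (true values 0.20 and 0).

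**Missing follow-up.** Suppose 20% of participants supply baseline only, spread evenly over conditions; this is the limit of the 80% retention benchmark. Under compound symmetry the 64 completers carry weight 64 × 3/(1 + 2r) and the other 16 carry weight 16 at expectation zero.

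- r = 0.5: 0.267 × 96/(96 + 16) = 0.229.
- r = 0.8: 0.267 × 73.8/(73.8 + 16) = 0.219.

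The crossed model still targets 0.40.

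**Power, illustrative, complete data, sustained 0.40 SD interaction.** As written: effect 0.267, SD √((1 + 2r)/3). Crossed, baseline left free: effect 0.40, SD √(2(1 − r)). Crossed, baseline means constrained equal: effect 0.40, SD √(1 − r²). Each SD is multiplied by √(2/40) to give the standard error.

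| r | As written | Crossed, baseline free | Crossed, baseline constrained |
|---|---|---|---|
| 0.3 | 0.37 | 0.33 | 0.47 |
| 0.5 | 0.31 | 0.43 | 0.54 |
| 0.7 | 0.27 | 0.64 | 0.71 |
| 0.8 | 0.25 | 0.81 | 0.85 |

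At r = 0.5, for example, the written model gives 0.267/(0.816 × 0.224) = 1.46 and Φ(1.46 − 1.96) = 0.31. The first two columns cross where (4/9)/((1 + 2r)/3) = 1/(2(1 − r)), that is at r = 5/14 ≈ 0.36.

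**The case against.** The strongest reply is that the list of fixed effects is not exhaustive. It omits component-by-time terms too, and these enter only through the following sentence. The article condenses a fuller plan, nothing in it excludes three-way terms, and crossing the count variable with time suggests that combination effects were meant to be followed over time. This stands in part: the authors may well have intended the three-way terms, and a reader who infers that they deliberately excluded them goes beyond the text. But the sentence that supplies the crossing does so for single components, so an analyst following it would fit the model examined here. The article fixes which terms are crossed with time; this is not mere detail left to an analysis plan.

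Three other stronger readings are tempting and are not supported.

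- *The written model always loses power.* Below r of about 0.36 the uncrossed term has slightly more power than the change contrast, and the article gives no correlation.
- *The 80% power claim is wrong.* The scale of the 0.40 is not stated, and the figure can be reached under some correlations. Failure to reproduce it does not show an error.
- *Crossing with time removes chance baseline imbalance.* It does not if baseline is left free. Under compound symmetry an imbalance b shifts the written estimate by b(1 + 2r)/3 and the change contrast by −b(1 − r); at r = 0.5 these are 0.67b and −0.50b.

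**Conclusion.** The point holds for the model as written. Each two-way component interaction is a single time-constant coefficient that pools the pre-treatment visit, and no interaction specific to post-intervention or 3 months can be estimated.

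The exact fractions, two thirds for a sustained interaction and one third for one confined to post-intervention, require compound symmetry and complete data. Other covariance structures or dropout change the weights but still bring baseline in. That conclusion does not depend on the correlation or on how the 0.40 is read. The power figures do depend on both and are illustrations only. The reason to act is that the fitted term answers a different question from the one the trial needs for choosing a combination.

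**What to change.** Add the three component-by-component-by-time terms, each with two time indicators, and state that interactions at post-intervention and at 3 months are tested from them, as is already done for single components. If these terms were always intended, one sentence saying so is enough.

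Optionally, constrain baseline means to be equal across conditions, which randomisation justifies. The last column of the power table needs this constraint; adding the three-way terms alone gives the middle column.

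The cost is one line of model specification and six more fixed-effect parameters, with no change to data collection. If baseline is left free, power for a sustained interaction is slightly lower than in the written model when the within-person correlation is low (0.33 against 0.37 at r = 0.3).

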## Materials and Methods

### Participants and Recruitment

Across both parts of the study, participants will be survivors of a non-metastatic gynecologic cancer who have completed primary treatment, are between the ages of 18 and 74, and report poor sleep quality. Part 1 of the study will include 15 participants and Part 2 will include 80, for a total sample size of 95 participants to be enrolled over 5 years. Participants will be recruited from the Robert H. Lurie Comprehensive Cancer Center of Northwestern University and the University of Arizona Cancer Center, two comprehensive cancer centers located in Chicago, IL and Tucson, AZ, United States, respectively. All potential participants will provide verbal consent to complete screening for study eligibility. Those who are eligible and subsequently enroll will provide written informed consent prior to engaging in any study activities.

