### Study Design

This two-part study is guided by the MOST framework. Participants in Part 1 will not be randomized, but rather will receive all three candidate intervention components simultaneously. It is well established that greater adherence predicts behavioral sleep intervention efficacy; however, knowledge of how best to increase adherence is limited (Matthews et al., 2012, 2013; Agnew et al., 2021). Therefore, upon completion of the intervention in Part 1, individual semi-structured interviews will be conducted with participants and analyzed to identify barriers to and facilitators of adherence to the three candidate intervention components. Results will inform the design and delivery of the components in Part 2 to enhance adherence. Subsequently, in Part 2, a full factorial experiment will be completed that involves eight experimental conditions (Table 1). It is important to note that this study is not an eight-arm RCT and the purpose is not to compare outcomes across each of the eight conditions directly. Rather, each main effect and interaction estimate will use data from participants in all of the experimental conditions. For example, the main effect of sleep restriction will be estimated by comparing the mean for the 40 participants in conditions 1 through 4 to the mean for the 40 participants in conditions 5 through 8 in Table 1. A detailed explanation of how factorial study designs maintain power has been previously published (Collins et al., 2009).

**TABLE 1 T1:** Experimental conditions.

Experimental condition	Sleep restriction	Stimulus control	Bright light
1	Yes	Yes	Yes
2	Yes	Yes	No
3	Yes	No	Yes
4	Yes	No	No
5	No	Yes	Yes
6	No	Yes	No
7	No	No	Yes
8	No	No	No

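### Because baseline is modelled as an outcome with free component differences, each Part 2 component effect is a change-from-baseline contrast: unbiased, but generally less precise than a common-baseline or baseline-adjusted estimate

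*Protocol article*

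**What the plan says.** The Protocol article, section Part 2: Intervention Optimization, sets out one longitudinal mixed model per outcome.

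- Baseline is part of the response: "All study time points will be included in these models, and fixed effects will include time".
- Time is "a nominal variable with three levels, which will be entered as two indicator variables".
- The other fixed effects are "each candidate intervention component, and two-way interactions among components", with components coded −1 and +1.
- The tested term is named: "The effect of a component at post-intervention and 3-month follow-up will be assessed based on" the component-by-time interaction (the effect "will be assessed based on that component’s interaction with time").

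The models also adjust for the listed covariates and for baseline characteristics that turn out to differ significantly between conditions. The baseline value of the outcome is not named as a covariate, and no constraint on baseline means is stated. A further model replaces the components by the number of components received, again as a fixed effect together with its interaction with time.

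The power statement in the same section is "to detect an effect size ≥0.40 for main effects and two-way interactions with 80% power and two-sided alpha = 0.05". Participants and Recruitment gives the size: "Part 1 of the study will include 15 participants and Part 2 will include 80". Study Design describes a main effect as "comparing the mean for the 40 participants in conditions 1 through 4 to the mean for the 40 participants in conditions 5 through 8".

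**The concern.** When baseline is the reference time, the component term in this model is a baseline difference between participants who will and will not receive the component. The model estimates that difference freely and measures the treatment effect relative to it.

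Yet Part 2 is randomised. The article also places the baseline assessment ahead of the orientation session (Treatment Expectancy), and the orientation is where participants hear which components they will receive (Intervention Delivery). The true baseline means are therefore equal across conditions, and estimating differences between them uses up information.

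The planned covariates do not restore it. With complete data, a covariate that is constant over time and enters as a main effect leaves the component-by-time contrast unchanged.

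Precision matters here because components are kept or dropped on these estimates, each resting on 40 against 40 participants at most. Avoidable imprecision could cause an active component to be discarded. The number-of-components model has the same structure and shares the weakness.

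**Working it through.** **Inputs from the article.** N = 80, 40 against 40 for a main effect; two-sided alpha 0.05; effect size 0.40, scale not defined; 80% retention as a feasibility benchmark.

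**Assumed, because the article does not give them.** Baseline as the reference time; 0.40 as a standardised mean difference on the follow-up SD; pre-post correlation r from 0.3 to 0.9; k = baseline SD / follow-up SD, set to 1 unless stated.

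**1. The article's own power figure.** With no use of baseline, the standard error is √(1/40 + 1/40) = 0.2236 SD and the noncentrality is 0.40/0.2236 = 1.79. Power is 43% (normal) or 42% (t on 80 − 7 = 73 df), and 80% would need 99 per level. Reading 0.40 as a coefficient on the −1/+1 scale doubles the difference to 0.80 and gives 94–95%. The stated 80% needs a variance factor of about 0.397. For a change contrast, 2(1−r) = 0.397 gives r ≈ 0.80. With baseline adjustment, 1−r² = 0.397 gives r ≈ 0.78. The article states no correlation.

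**2. Variances, in units of the follow-up variance.**
- Planned contrast (change from baseline): 1 + k² − 2rk
- Common baseline or baseline-adjusted: 1 − r²
- Planned minus alternative: (k − r)², which is never negative and is zero when k = r
- Ratio (alternative/planned): (1 − r²)/(1 + k² − 2rk)
- With k = 1: (1 − r²)/[2(1 − r)] = (1 + r)/2

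**3. Equal SDs, d = 0.40.** The standard error is √(0.05 × variance factor).

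| r | Planned 2(1−r) | Alternative 1−r² | Ratio | Power, 80 complete | Power, 64 complete |
|---|---|---|---|---|---|
| 0.3 | 1.40 | 0.91 | 0.65 | 32% → 46% | 26% → 38% |
| 0.5 | 1.00 | 0.75 | 0.75 | 42% → 53% | 35% → 44% |
| 0.7 | 0.60 | 0.51 | 0.85 | 63% → 70% | 53% → 60% |
| 0.8 | 0.40 | 0.36 | 0.90 | 80% → 84% | 70% → 75% |
| 0.9 | 0.20 | 0.19 | 0.95 | 97.7% → 98.2% | 94% → 95% |

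The 64 is 80% of 80. At r = 0.5 the planned contrast has the same variance as ignoring baseline; below 0.5 it has more.

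**4. Unequal SDs (illustrative).**
- k = 0.7, r = 0.5: 0.75/(1 + 0.49 − 0.70) = 0.75/0.79 = 0.95, against 0.75 with equal SDs.
- k = 0.8, r = 0.7: 0.51/(1 + 0.64 − 1.12) = 0.51/0.52 = 0.98, against 0.85.
- With k above 1 the gain is larger than in the table.

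**5. Simulation of the 2×2×2 design.** N = 80, 1,500 runs per setting, equal SDs, generalised least squares with a known equal-correlation covariance.
- Complete data: the planned component-by-time estimate equals the change-score regression estimate to about 2 × 10⁻¹⁵. The common-baseline variance is 0.73, 0.83 and 0.92 of the planned variance at r = 0.5, 0.7 and 0.8 (theory 0.75, 0.85, 0.90). Both estimators are centred on the true effect.
- About 20% dropout, missing at random: the planned estimate correlates 0.97 to 0.99 with the change-score contrast. The variance ratios are 0.79, 0.90 and 0.96.

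**The case against.** The strongest reply is that nothing here is invalid. The planned model is a conventional one, its contrast is unbiased under randomisation, and preferring a more efficient model can look like a reviewer's taste. An analysis plan that is not shown might also refine the specification. The first part stands: this is lost efficiency, not bias, and a reader who inferred that the planned estimates are biased would go beyond the text. The second part carries less weight, because the article itself lists the fixed effects and names the tested term.

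The size is also open to challenge, and much of that challenge stands. A reader might infer that the alternative gains precision at every r below 1. That holds with equal SDs but not in general, since there is no gain when k = r. Entry requires a PSQI score above 5 (Eligibility), which could narrow the baseline spread and pull k below 1. The gain is small at r of 0.8 or above, which is where the stated 80% power would be met if 0.40 is a standardised difference. Dropout reduces it further: at r = 0.5 the gain is worth about 33% more participants with complete data (1/0.75) but about 27% with 20% dropout (1/0.79). The 80% retention figure is a feasibility benchmark, not an attrition forecast.

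The identity with a change score is exact only for complete data with baseline as the reference time. With dropout, or if pain (measured at all three visits) enters as a time-varying covariate, it is an approximation.

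A reader might also conclude that the stated 80% power is wrong. The documents do not support that. The figure cannot be reproduced from the stated inputs alone, but the calculation may have used a pre-post correlation or an effect-size scale that the article does not report.

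**Conclusion.** The point holds as one of efficiency. As written, the model estimates baseline differences that randomisation makes zero in truth, and no stated covariate recovers the precision spent on them. A common-baseline or baseline-adjusted analysis is valid here and, in large samples, never less precise.

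How much it gains cannot be fixed from the documents, which give neither r nor k. With equal SDs and complete data the variance saving is (1−r)/2: 35% at r = 0.3, 25% at 0.5, 15% at 0.7, 10% at 0.8 and 5% at 0.9. With about 20% dropout the simulated saving is about 21%, 10% and 4% at r = 0.5, 0.7 and 0.8. It could be near zero if k is close to r, or larger than these figures if k exceeds 1. The change is worth making because it costs almost nothing, not because the planned analysis would mislead.

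**What to change.** In the Part 2 mixed models, constrain baseline means to be equal across conditions. Drop the time-constant component and component-product terms, and keep time, component-by-time and component-product-by-time at the two follow-ups. The product-by-time terms should be written out, because once the time-constant products are dropped they alone carry the two-way interactions. Leave the covariance over the three visits unrestricted, so that the weight given to baseline is estimated and the result does not rely on equal SDs.

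An alternative is to model only the two follow-ups, with the baseline outcome (by time) as a covariate. The two approaches are similar but not identical when baseline or follow-up values are missing, so the plan should name one.

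Make the same change in the number-of-components model: drop its time-constant term and keep its interaction with time. State the assumed pre-post correlation and the effect-size scale beside the power figure.

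The cost is a change of model specification, with the same data and the same software. It should be recorded before outcome data are analysed, so that the choice cannot appear to follow the results.
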